### Measurement of the hematoma volume

The ABCs method is adopted to measure the hematoma volume: Volume(ml) = (A × B × C)/2[25]. “A” is the long axis of the hematoma on the CT slice where the hematoma has the largest area. “B” is the longest axis of the hematoma perpendicular to the long axis on the same CT slice. “C” is the product of the interslice distance and the count of slices on which the hematoma is visible. The intraventricular hematoma is not counted. The rebleeding or hematoma expansion is defined as a 10 ml increase between two CT scans.

### Treatments

#### *Endoscopic surgery group*

This group of patients will receive endoscopic surgery and the best medical treatment. The surgery will be performed as soon as possible after the randomization, and the medical treatment will be started immediately. Neurosurgeons will decide surgical approaches according to the location, size, and shape of hematomas. The hematomas will be evacuated as much as possible with the help of the angled endoscope, but the stiffly attached clot won’t be removed by force in order to prevent unnecessary damage, and the restricted intracavity operation will be the principle during the hematoma evacuation.

A “Rebleeding test” will be performed after the hemostasis. For patients with hypertension, the blood pressure will be slowly elevated to the level before the anesthesia, and for other patients, a raise of 20 ~ 30 mmHg will be gained. The anesthetist will maintain this level of blood pressure for 10 minutes. Only if there is no new bleeding site, neurosurgeons can start to close.

#### *Conservative treatment group*

The best medical treatment will be provided to this group of patients right after the admission. A “multistep blood pressure control” will be carried out. The range of the first reduction is limited to 20% of the admission level for patients with hypertension, and it should be accomplished in half an hour. If the patients' systolic blood pressure exceeds 225 mmHg, the goal is lower than 180 mmHg. The level of blood pressure will be maintained for 8 hours and gradually reach the normal standard in 72 hours.

After patients are stabilized, the rehabilitation will be started as early as possible.

### Follow-up

Patients will be followed up at 1, 3, and 6 months after initial treatment.

### Outcome assessment

Both investigators have been trained at least 20 hours by multimedia, bedside practice, and a qualification exam, before they start to evaluate patient outcomes.

#### *Primary outcomes*

The primary outcomes of the study are the Extended Glasgow Outcome Scale (GOSE)[26] and the Modified Rankin Scale (mRS) at 6 months after initial treatment. Both scales will be measured with structured interviews.

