### Sample size

The rate of the favourable outcome of patients with basal ganglia hemorrhage is about 30% for conservative treatment [5,6] and 60% for endoscopic surgery [22-24]. A sample size of 86 will be required with a significance level of 5% (2-sided) and a power of 80%. In consideration of the loss to follow-up, the sample size is enlarged to 100.

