### Statistical analysis

Both Intention To Treat (ITT) and Per-Protocol (PP) analysis will be performed. The level of significance is 0.05, and Power is 80%. The quantitative data will be analyzed by *t*-test. Chi-square test will be used to analyze the categorical data. For the ordinal data, Wilcoxon rank test is adopted. And survival analysis will be carried out for further comparison of mortality. Logistic regression will be used to adjust the effect of multivariables.

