## Discussion

Spontaneous basal ganglia hemorrhage is very likely to cause death, independence, disability, and lead to a great financial burden, so it’s always a hot issue in neurology and neurosurgery. There are already more than 10 randomized controlled trials referring to the treatment choices of SICH, but we still designed this study due to the following reasons. A). To evacuate or not, it’s controversial, especially for moderate-volume hematomas. B). It’s reasonable to evacuate the hematoma considering its mechanical, chemical, and biological harm to the brain tissue [8-10]. C). As a minimally invasive technique, endoscopic surgery may reveal the benefit of the hematoma evacuation, which is probably covered by the secondary injury caused by traditional craniotomy. D). There is a lack of randomized controlled trial focusing on endoscopic surgery for the moderate-volume hematoma in spontaneous basal ganglia hemorrhage.

For patients in the conservative treatment group, if their condition deteriorates because of hematoma expansion or rebleeding during the trial, and the surgical indications are clear, then hematoma evacuation should be performed. The crossover will be analyzed in both ways: ITT and PP.

Surgical approaches for the hematoma evacuation in the basal ganglia include the temporal approach, the frontal approach, and the transsylvian approach. The last one is often performed under the microscope, so it won’t be applied in this study. The temporal approach usually provides the shortest distance from the cortex to the hematoma, but it may cause injury to the visual pathway, and if the hematoma is elliptical, neurosurgeons may fail to evacuate the frontal part of the hematoma because of the blind angle. In the frontal approach, the trajectory of endoscope is parallel to the long axis of the hematoma, so neurosurgeons get a better view through this approach, and it’s advised to be used for hematomas larger than 50 ml [27]. However, for small and moderate volume hematomas, much further distance is needed to reach them by the frontal approach, which means more brain tissue damage. Also, the aspect ratio of moderate-volume hematomas is more approximate to 1:1 than the large ones, which makes fewer blind angle through the temporal approach. In this study, surgical approaches will be decided according to the location, size, and shape of hematomas.

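### Two unranked primary outcomes share one 5% level and a sample size for a single comparison, with no either/both rule, so the stated 5% and 80% are not both secured

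*Protocol article*

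**What the plan says.** The Primary outcomes section of the protocol article names "the Extended Glasgow Outcome Scale (GOSE)[26] and the Modified Rankin Scale (mRS) at 6 months after initial treatment" and does not rank them. The Abstract also lists both as primary.

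The Sample size section plans for one favourable-outcome rate, 30% under conservative treatment and 60% under endoscopic surgery, without naming the scale or cut-off: "A sample size of 86 will be required with a significance level of 5% (2-sided) and a power of 80" per cent. It then adds: "In consideration of the loss to follow-up, the sample size is enlarged to 100".

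The Statistical analysis section gives one level for the whole trial: "The level of significance is 0.05, and Power is 80" per cent. It also says: "Both Intention To Treat (ITT) and Per-Protocol (PP) analysis will be performed". The Discussion repeats the pair for patients who cross over to evacuation: "The crossover will be analyzed in both ways: ITT and PP".

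The article has no either/both rule, no testing order and no division of the 5%.

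**The concern.** With two primary outcomes, what alpha and power mean depends on the success rule. If a significant result on either scale counts, there are two chances of a false positive at 0.05 each, and the trial-level error exceeds 5%. If both scales must be significant, the error is contained, but the chance of passing both tests is lower than the chance of passing one, and the sample size was worked out for one. With no rule written down, neither figure can be taken at face value.

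The practical risk arises when the scales disagree. The plan would let a significant result on one scale be reported as a positive primary result, and nothing in it would settle the dispute. The sample-size paragraph cannot break the tie, because it does not say which scale defines a favourable outcome.

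**Working it through.** **Inputs.** From the Sample size section: rates 0.30 and 0.60, two-sided alpha 0.05, power 0.80, N = 86 enlarged to 100. From Primary outcomes: two scales. Assumed, because the article does not give them: 1:1 allocation, the 30%/60% rates applying to each scale, and a correlation r between the two test statistics of 0.8 to 0.95.

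**1. The plan's own N.** For two proportions with pooled variance under the null and no continuity correction:

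n per arm = [1.960 × √(2 × 0.45 × 0.55) + 0.842 × √(0.30 × 0.70 + 0.60 × 0.40)]² / 0.30² = 3.777 / 0.09 = 41.97, so 42 per arm and 84 in total.

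This is within two patients of 86. (Unpooled variance gives 80, and a continuity correction gives 98.) The stated N is thus reproduced with the whole 5% spent on one comparison. Power at 43 per arm is Φ[(0.30 × √43 − 1.960 × √0.495) / √0.45] = Φ(0.877) = 0.810.

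**2. Either scale can win, no adjustment.** Family-wise error = 1 − P(|Z1| < 1.96 and |Z2| < 1.96), with Z1 and Z2 bivariate normal with correlation r. Independent tests would give 1 − 0.95² = 0.0975, an upper reference.

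**3. Both scales must win.** Joint power = Φ₂(a, a; r), where Φ(a) is the power per scale. Then a = 0.842 for 80% power, and a = 0.877 at 86 evaluable. At 100 evaluable, power per scale is 0.866.

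| r | Error, either wins | Joint power, 80% per scale | Joint power, 86 evaluable | Joint power, 100 evaluable |
|---|---|---|---|---|
| 0.80 | 0.078 | 0.729 | 0.741 | 0.81 |
| 0.90 | 0.070 | 0.750 | 0.761 | 0.83 |
| 0.95 | 0.065 | 0.765 | 0.775 | 0.84 |

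Stepping the number evaluable up two at a time, joint power first passes 80% at 98 patients (r = 0.8), 94 (r = 0.9) or 92 (r = 0.95).

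**4. Either scale can win, with adjustment.** Bonferroni tests each scale at 0.025 (critical value 2.241). The step 1 formula then gives 50.96, so 51 per arm and 102 evaluable for 80% power per scale. At 86 evaluable, power per scale is Φ(0.582) = 0.720. At 100 evaluable it is 0.791.

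The chance of winning on at least one scale is higher. At 86 evaluable it is 2 × 0.720 − Φ₂(0.582, 0.582; r) = 0.81, 0.78 and 0.76 for r = 0.8, 0.9 and 0.95. With Hochberg, by simulation (2 million draws), it is 0.82, 0.80 and 0.79.

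**The case against.** The strongest reply is that a condensed article commonly leaves multiplicity rules to the full protocol or the analysis plan, which are not shown, so an unseen rule may settle the matter. That holds for the rule itself. It does not fully answer the point, because the primary outcomes and the sample size are fixed in this article, and any rule added later has to fit them. A both-must-win rule gives less than 80% at the planned 86 evaluable. A Bonferroni split gives 72% per scale, although the chance of winning on at least one scale stays near 80%. Naming one scale first keeps both figures for that scale, but it departs from the two equal primary outcomes stated here.

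Three further limits stand:

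- The effect is modest. The two scales both grade global disability and should seldom disagree, so the excess error is about 1.5 to 2.8 percentage points, under correlations that the article does not give.
- The power shortfall is conditional. If all 100 patients are evaluable, joint power is 81% to 84%. Full retention is not what was planned, since the extra 14 patients are there to cover loss to follow-up.
- Power per scale is not firmly established. The sample-size paragraph names no scale, and the Statistical analysis section assigns a rank test to ordinal data, so a two-proportion calculation may not describe the test used on either scale.

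A reader might also infer that ITT and PP have equal standing, giving four chances to claim success and a still larger error. The text does not support that. It says both analyses will be done, but not that PP can carry the efficacy claim. ITT is listed first both times, and in the Discussion the pair is tied to crossover, which suggests a sensitivity purpose. No four-test error rate is claimed here.

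**Conclusion.** The point stands as a missing decision rule set against a sample size for one comparison. The 5% and the 80% are not both secured by the plan as written. If either scale can win without adjustment, the family-wise error is about 7.8% to 6.5% for r = 0.8 to 0.95. If both must win, joint power is about 73% to 76% with 80% on each scale, and 74% to 78% at 86 evaluable.

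It would go too far to say that the 5% level is breached. Under a both-must-win rule the error stays at or below 5%, and the cost falls on power. What can be said is that the error rate is not controlled by anything in the article. The power figures at 86 and 100 evaluable also rest on 1:1 allocation and on the 30%/60% rates holding for both scales.

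**What to change.** Name one of the two scales, with the cut-off that defines a favourable outcome, at 6 months in the ITT population as the single primary outcome tested at two-sided 0.05. Make the other scale the first secondary outcome, or test it second in a fixed order only if the first is significant. State that PP is supportive. Nothing in the article ranks one scale above the other, so the choice is the sponsor's. It should be recorded before the database is locked.

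This is a wording change. Alpha, N and data collection stay as they are, and the cost is that one scale loses the primary label.

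If both scales are to stay primary, choose one of these:

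- State that both must be significant at 0.05, and restate the power (74% to 78% at 86 evaluable under the assumptions above) or raise N.
- State that either can win under Hochberg or Bonferroni, and restate the power, saying whether it is per scale (about 72% at 0.025 with 86 evaluable) or for at least one scale. Keeping 80% per scale under Bonferroni needs about 102 evaluable patients, more than the 100 to be enrolled.

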#### *Secondary outcomes*

The secondary outcomes include the National Institutes of Health Stroke Scale(NIHSS) and the mortality after 6 months since initial treatment.

#### *Other outcome*

The Barthel Index (BI) will also be evaluated.

### Ethics

This study is conducted in accordance with the Declaration of Helsinki and guideline for Good Clinical Practice. All patients and their relatives are fully informed about the trial, and they have had a copy of the informed consent form. The trial is approved by the Biological and Medical Ethics Committee (BMEC) of West China Hospital (2011Reviewed-No.92).

### Data collection and management

The allocation data of patients is kept by the trialist who specializes in randomization. Neurosurgeons should fill in CRF except the follow-up forms, which must be completed by another two investigators trained for outcome assessment. Double input will be used in the data entry. The QMB and the principal investigator will check and examine the data, then the database will be locked and sent to a statistician.

### Adverse and severe adverse events

Adverse event (AE) is any undesirable incident happening to patients during the study. It will be recorded on CRF, including a description of the event, the correlation with the trial, the starting date, the ending date, actions taken and their efficacy, and the patient outcome. Severe adverse event (SAE) is defined as the event of death or vegetative state. Severe disability is not included, because basal ganglia hemorrhage tends to cause severe disability. SAE will also be recorded on CRF. All AEs and SAEs will be reported to the QMB and the BMEC, and the time limit for SAE report is 24 hours.

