## Background

Spontaneous intracerebral hemorrhage (SICH) is a disease with high morbidity, high disability rate, high mortality, and high economic burden [1,2]. Its annual incidence is about 20 cases per 100,000 population [3,4]. More than 70% patients end up with death or dependence [5,6].

The main clinical management of SICH includes surgical and medical treatment. Whether patients can benefit from surgery is still controversial, especially for those with basal ganglia hemorrhage, which is the major subtype of SICH [7]. Surgical evacuation of hematomas can relieve the mass effect and reduce the harmful substance released during their coagulation, liquefaction, and resolution [8-10], but surgical procedures may also injure the brain tissue, and cause other operative complications. These disadvantages reduce the benefit of surgery. Some clinical trials were carried out to compare surgery with medical treatment. The most famous trial is the STICH trial conducted by Mendelow et al. [5]. 1033 patients were randomized. After 6 months follow-up, 26% of patients in the early surgery group had a favourable outcome compared with 24% in the group of initial conservative treatment. Early surgery did not show significant advantages. However, in this study less than 25% of the operations were minimally invasive. Trials of stereotactic surgery or craniopuncture were also carried out [11-13]. But none of the trials and systematic reviews provide sufficient evidence for the choice of treatments [6,14-16].

In clinical practice, neurologists and neurosurgeons tend to choose conservative treatment for patients with small-volume hematomas, and surgery for those with large-volume hematomas [17]. However, when the volume of the hematoma exceeds 60 ml, neither of the methods give much help [18]. Treatments for moderate-volume hematomas have the most uncertainty. Some recently randomized trials indicate these patients may benefit from minimally invasive surgery [13,19]. Kim et al. [19] randomized 387 patients with basal ganglia or thalamus hematomas to stereotactic-guided evacuation (group A) or conservative treatment (group B), and the mean hematoma volume was 23.1 ml. At the end of 6 months follow-up, the mean score of modified Barthel index was 90.9 in group A and 62.4 in group B, and the mean score of modified Rankin scale was 1.2 in group A and 3.0 in group B. Patients received stereotactic-guided evacuation had better clinical outcomes and motor function.

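### Only death and vegetative state trigger the 24-hour report, so serious events that the patient survives, including surgical ones, reach oversight with no stated deadline

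*Protocol article*

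**What the plan says.** The section on adverse and severe adverse events in the protocol article sets up two tiers.

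- **Adverse events (AEs).** The definition is broad: "Adverse event (AE) is any undesirable incident happening to patients during the study". The record is detailed: "It will be recorded on CRF, including a description of the event, the correlation with the trial, the starting date, the ending date, actions taken", followed by the efficacy of those actions and the patient's outcome.
- **Severe adverse events (SAEs).** The definition is closed: "Severe adverse event (SAE) is defined as the event of death or vegetative state". One exclusion is explained: "Severe disability is not included, because basal ganglia hemorrhage tends to cause severe disability".
- **Reporting.** "All AEs and SAEs will be reported to the QMB and the BMEC, and the time limit for SAE report is 24 hours". No limit is given for AEs that are not SAEs.

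Elsewhere the article treats non-fatal harm as relevant. The Background says that "surgical procedures may also injure the brain tissue, and cause other operative complications". The section on hematoma volume gives a measurable criterion: "The rebleeding or hematoma expansion is defined as a 10 ml increase between two CT scans". The treatment section requires a rebleeding test before closure in the surgical arm. The Discussion describes tissue injury linked to the surgical approaches, and it expects that some conservatively treated patients will deteriorate through expansion or rebleeding.

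**The concern.** An expedited report exists so that the oversight bodies learn of serious harm early enough to act on it. Here the trigger is an end state, not the event that may lead to it. A patient who rebleeds after endoscopic evacuation, is operated on again and survives with some awareness never meets the definition. If a rebleed later ends in death, it is the death that meets the definition, and the earlier event had no deadline.

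The stated reason is sound only for disability that the index hemorrhage would be expected to cause. As written, the exemption is not limited in that way. It also removes new severe disability caused by the procedure. It gives no reason for leaving out rebleeding, reoperation or serious operative complications.

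At stake is the timeliness of safety oversight. A cluster of serious surgical events could build up while nothing in the stated rules requires prompt notice to the Quality Monitoring Board or the ethics committee.

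**Working it through.** The plan gives no figure on this point, so there is none to reproduce. The check is to take each kind of event and apply the stated rules.

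| Event | SAE as defined? | 24-hour limit stated? | Recorded and reported as an AE? |
|---|---|---|---|
| Death | Yes | Yes | Reported as an SAE |
| Vegetative state | Yes | Yes | Reported as an SAE |
| Rebleeding or expansion (10 ml criterion), survived and not vegetative | No | No | Yes |
| Reoperation, survived and not vegetative | No | No | Yes |
| Serious operative complication, survived and not vegetative | No | No | Yes |
| New severe disability due to the procedure | No, expressly excluded | No | Yes |

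The last four rows are the gap. Next, compare the gap with the reason given. The reason refers to severe disability only, so it can bear on the last row alone. Even there it fits only disability attributable to the index hemorrhage.

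**Illustrative size.** Inputs: the enlarged total of 100 patients (Sample size section), and equal allocation, which the article does not state, giving 100 / 2 = 50 per arm. The rate of serious non-fatal complications is assumed, with a range of 5% to 15%. Affected surgical patients = 50 × rate:

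- 50 × 0.05 = 2.5
- 50 × 0.10 = 5
- 50 × 0.15 = 7.5

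These counts show how many surgical patients would have an event in the AE tier and not the SAE tier. They do not count lost data. Non-fatal expansion in the conservative arm would add to them by an amount that the documents do not allow one to estimate.

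**Can harm still be compared by arm?** The data exist, because every such event is an AE in either arm. For illustration, take 50 per arm, a two-sided 5% test, z = 1.96, p̄ = (p₁ + p₂)/2 and

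power = Φ{ [ |p₁ − p₂|√50 − z√(2p̄(1 − p̄)) ] / √(p₁(1 − p₁) + p₂(1 − p₂)) }.

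For assumed rates of 5% and 10%: (0.354 − 0.730) / 0.371 = −1.02, so power is about 16%. The same formula gives 38% for 5% against 15%, 62% for 5% against 20%, and 81% for 5% against 25%. The comparison is possible, though imprecise unless the difference is large. That limit comes from the sample size and not from the SAE definition.

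**The case against.** The strongest reply is that nothing is hidden. Every undesirable event is an AE, is recorded with dates, relation to the trial, actions and outcome, and goes to both oversight bodies. Rebleeding has a measurable criterion, and the statistical section names a test for categorical data. Lasting harm from surgery should also show in the 6-month functional scales and in mortality. All of this stands, and it rules out three stronger readings that a reader might be drawn to.

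- **That surgical harm cannot be compared between arms.** The AE records supply the data. How they are tabulated is commonly left to an analysis plan, which is not shown here, so its absence is no finding.
- **That the benefit-harm conclusion is tilted toward surgery.** The definition applies equally to both arms, and the article itself expects expansion or rebleeding under conservative treatment. The reporting category changes no efficacy estimate.
- **That the definition contradicts the Ethics section.** That section says "This study is conducted in accordance with the Declaration of Helsinki and guideline for Good Clinical Practice", but the guideline's own definition of a serious event is not in the documents, so a contradiction cannot be shown from them.

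It can also be said that a fuller protocol might set a deadline for AEs. That is possible. However, the SAE definition is stated in full and closed at two items, so the shortness of an article does not explain it. The reply therefore leaves the deadline gap in place.

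**Conclusion.** The point holds in a limited form. Followed as written, the rules require 24-hour notice only of death and vegetative state. Serious non-fatal events in either arm, including surgical ones, arrive as ordinary AEs with no stated deadline, and the reason given covers only part of what is left out. This is a weakness in the speed of safety oversight. It is not a loss of data, a bias in the efficacy result or a bar to comparing harm.

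The illustrative size of 2.5 to 7.5 surgical patients rests on equal allocation and an assumed rate of 5% to 15%. The conclusion does not depend on it, because it follows from the definition alone. The change is worth making on safety grounds and ranks below the faults that must be repaired before the trial's main result can be relied on.

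**What to change.** Revise the SAE definition in the section on adverse and severe adverse events as follows.

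1. Besides death and vegetative state, include any event that is life-threatening, needs re-intervention, prolongs hospitalisation, or causes new disability not explained by the index hemorrhage.
2. Name rebleeding or hematoma expansion (by the article's existing 10 ml criterion), reoperation and intracranial infection as reportable within 24 hours in both arms.
3. Keep the exemption for severe disability, but limit it expressly to disability expected from the index hemorrhage.

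The cost is one protocol paragraph and a larger number of 24-hour reports, for events that the case report form already captures as AEs. Someone must also judge whether a new disability is explained by the index hemorrhage. Outcomes, sample size and efficacy analyses are unchanged.
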